### Randomization

2.6

A total of 148 subjects with KOA who are eligible per protocol will be randomly assigned to group A - Jade moxibustion group or group B - traditional moxibustion group in a 1:1 ratio. The subject will first receive a brief phone consultation, after that, the subject will be allocated to the site. After the investigator and the subject signed the informed consent, the investigator will perform a simple rheumatic examination. The investigator will make a diagnosis based on the knee x-ray film brought by the subject or the knee X-ray performed at site. Only the subject who meet the inclusion/exclusion criteria will be randomized by central network randomization program. Then investigator will make baseline assessment and arrange treatment.

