### Inclusion criteria

2.3

1.Age 50 to 75 years old.2.According to the American College of Rheumatology Diagnostic Criteria for KOA.^[22–26]^3.Radiologic confirmation of KOA (Kallgren-Lawrence level ≥1).^[27]^4.Moderate or greater knee pain on most days of the past month; the subject's visual analog scale baseline score for arthritic pain is 40 points and above.5.Agreed to be randomly assigned, understand and would like to sign an informed consent.

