### Primary outcome indicators

3.1

The primary outcome measure is the change in pain relative to baseline at the Western Ontario and McMaster Universities Osteoarthritis Index (WOMAC) in 4 weeks. The most painful knee joint for the subject will be recorded at the baseline, which will be the joint we measured throughout the trial. We will also measure WOMAC pain at week 2, 8, 12, and 24.

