## Discussion

4

The purpose of this study is to explore an effective moxibustion replacement therapy, Jade moxibustion for KOA. The trial will evaluate its non-inferior efficacy compared with traditional moxibustion. Subjects will receive 3 times treatment a week. For Chinese medical external treatment, the frequency of 3 times a week is the most common treatment for KOA. One limitation of this trial is that due to different treatment instrument, the operators will know about the group allocation, which may lead to subjects’ bias. Therefore, study may use the expectation scale to measure the attitude of the subject to the treatment. The trail is aimed to provide reliable evidence for Jade moxibustion in the treatment of KOA, and to make up for the lack of clinical efficacy research in this field. Also, to provide reliable data for our future multicenter randomized clinical trial. Traditional moxibustion therapy produces heavy smoke with unpleasant smell. The smoke of moxibustion is considered as a biological hazard to health,^[37]^ which is therefore prohibited from use in many clinics and hospitals. Jade moxibustion is a new therapy based on the theory of TCM and is easy to operate with no smoke, which can be further explored for treatment amount and duration.

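### Section 2.6 places the baseline assessment after randomisation, while 2.2 and 2.3 imply it comes before, so the reference value of the primary outcome is not clearly protected from knowledge of allocation

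*Protocol article*

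**What the plan says.** Section 2.6 gives the only explicit order of steps in the article: telephone consultation, consent, a rheumatic examination, diagnosis from the knee X-ray, eligibility, randomisation. On the last two it says "Only the subject who meet the inclusion/exclusion criteria will be randomized by central network randomization program". The next sentence is "Then investigator will make baseline assessment and arrange treatment".

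Three other places bear on the order:

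- Section 2.2 (recruitment) describes an in-person visit, labelled as the baseline visit, after telephone screening, with radiography at about the same time.
- Section 2.3 requires for eligibility that the "visual analog scale baseline score for arthritic pain is 40 points and above".
- Section 2.7 stratifies by one or two affected knees.

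On the outcome, section 3.1 states "The primary outcome measure is the change in pain relative to baseline", measured on WOMAC at 4 weeks, and "The most painful knee joint for the subject will be recorded at the baseline, which will be the joint we measured throughout the trial". The opening of section 3 adds that, where both knees are eligible, the more painful one is evaluated.

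On blinding, the Discussion says that "due to different treatment instrument, the operators will know about the group allocation" and accepts that this may bias subjects. No blinding of subjects, investigators or assessors is described.

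**The concern.** A baseline value is balanced by randomisation only if it is fixed before anyone who can influence it knows the arm. WOMAC pain is the patient's own report. A patient pleased or disappointed by the allocation may rate current pain differently, and an investigator who knows the arm may prompt differently. Any difference between the arms that arises this way enters the primary outcome through its reference value.

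The same applies to the index knee where both knees qualify: the choice of the worse knee rests on a pain rating that, on the order in 2.6, may be made after allocation.

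This is a non-inferiority trial. A shift favouring the jade arm could support non-inferiority wrongly, and a shift the other way could hide it. Later adjustment cannot be relied on to remove the distortion, because the covariate would itself carry it.

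**Working it through.** No figure in the article tests this point, so the main check is to set the passages side by side.

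**Order of steps**

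| Place | What it implies |
|---|---|
| 2.6 | Eligibility, then randomisation, then baseline assessment, then treatment |
| 2.2 | A baseline visit within recruitment, with radiography. Since 2.6 puts the X-ray diagnosis before randomisation, this visit probably precedes it too |
| 2.3 | A baseline VAS score must exist before eligibility, hence before randomisation |
| 2.7 | The number of affected knees must be known at randomisation |
| 3.1 | The index knee is recorded at baseline; no timing relative to randomisation is given |

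Sections 2.2 and 2.3 cannot be squared with 2.6 unless baseline means two different things. No visible text places WOMAC, or the choice between two eligible knees, before randomisation. Figure 1 and Table 1 are not shown and cannot settle it.

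**Whether allocation can be known at that moment.** The last sentence of 2.6 has the same investigator assess baseline and arrange treatment. Nothing says that the allocation is withheld until the baseline forms are complete.

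**How a baseline shift reaches the outcome.** Let B be the true baseline, F the follow-up score and δ an arm-specific error in the recorded baseline, with F unaffected.

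- Absolute improvement: (B + δ) − F. The error passes through in full.
- Percentage response: section 3.5 cites a 36% change in WOMAC as effective. Read as improvement, response requires (B + δ) − F ≥ 0.36(B + δ), that is, B − F + 0.64δ ≥ 0.36B. Only 0.64 of the error counts.

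**Illustration only.** From section 3.5: effective rates of 55.56% (jade) and 46.51% (traditional), a difference of 55.56 − 46.51 = 9.05 points. Assumed, not in the documents: proportional improvement is normal with SD 0.25 to 0.35; the response rate without bias is 46.51%; the recorded baseline is overstated by a fraction s in one arm; F is unaffected; and the week-4 remission rate in section 3.6 means the 36% criterion. Then

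rate = Φ(Φ⁻¹(0.4651) + 0.64·s/SD), with Φ⁻¹(0.4651) ≈ −0.088.

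| s | SD 0.25: rate (gain) | SD 0.35: rate (gain) |
|---|---|---|
| 5% | 51.6% (+5.1 points) | 50.2% (+3.6 points) |
| 10% | 56.7% (+10.2 points) | 53.8% (+7.3 points) |
| 15% | 61.7% (+15.1 points) | 57.4% (+10.9 points) |

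Example: s = 0.10 and SD = 0.25 give −0.088 + 0.256 = 0.168, and Φ(0.168) ≈ 0.567. The table shows sensitivity. It does not say that a shift of any given size will occur.

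**The case against.** The strongest reply is that 2.6 is loosely worded and that the baseline measurements are in fact planned before randomisation. The visit in 2.2, the X-ray step it shares with 2.6 and the VAS criterion in 2.3 all support this, and the missing figure and table may confirm it. This stands in part: the article does not establish that WOMAC will be taken after allocation. It does establish a contradiction, and the only explicit sequence is the unsafe one. On either reading 2.6 has to change.

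A reader might also infer more than the documents support:

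- **That the protocol admits that everyone knows the arm.** The Discussion says only that "the operators will know about the group allocation". Treatment is given by an operator, while baseline is assessed by the investigator. That the patient or investigator could know the arm follows from the order of steps and the absence of described blinding. The article does not say it, nor does it use the term open-label.
- **That all change scores are exposed.** A VAS score precedes randomisation because eligibility depends on it, although the article does not say whether it also serves as the outcome baseline. Serum markers are laboratory values that reporting can hardly move. Section 3.6 compares secondary scores between groups at the follow-up times, and a comparison of follow-up scores alone needs no baseline.
- **That the index knee is open to influence in every patient.** With one eligible knee there is no choice, and the number of affected knees is already needed for stratification. Only patients with two eligible knees are concerned.
- **That the bias can be expressed as a share of the non-inferiority margin.** The article gives a cutoff of 0.5 and no other margin. The size of any baseline shift has no source in it either.

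**Conclusion.** The concern holds in this limited form: 2.6 conflicts with 2.2 and 2.3 on when baseline is measured. If 2.6 is followed as written, baseline WOMAC pain, and the index knee in patients with two eligible knees, can be recorded after allocation can be known. That can bias the primary comparison in either direction.

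The conclusion rests on the wording of 2.6, on the absence of any described blinding and on the visible difference between the treatments. Its size cannot be derived from the documents. The assumed shifts show only that a modest distortion, of 5% to 10% of baseline in one arm, would be of the same order as the difference used for planning. The point deserves correction before enrolment, because a baseline recorded after allocation cannot be repaired later.

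**What to change.** Reorder 2.6 as follows: consent; eligibility; baseline WOMAC, VAS, SF-36 and any expectation scale; recording of the index knee; locking of these entries; central randomisation and release of the allocation; first treatment. State that the randomisation system releases the arm only once the baseline entries and the index knee are confirmed.

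Align 2.2, 2.3, 2.6 and 3.1 so that baseline has one meaning, and say whether the VAS score used for eligibility is also the baseline for the VAS outcome. Check that Figure 1 and Table 1 show the same order.

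The cost is small: a few patients may complete the baseline questionnaires and then not be randomised. Sample size, outcomes and analysis are unaffected.

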### Stratification

2.7

The subjects will be stratified according to the number of lesions of the KOA (i.e., dual-joint and mono-articular).

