### Study setting, recruitment, and ethics

2.2

Recruitment will be carried out in Tongren Hospital Affiliated to Shanghai Jiaotong University and Shanghai Pudong Hospital of Traditional Chinese Medicine. A total of 148 subjects with KOA will be enrolled. The study was approved by the medical ethics review committees of Tongren Hospital (No. Tongren 2019-022-02). Recruitment will be carried out through social platform, out-patient department, community propaganda and other ways. Investigator will contact people who are willing to participate in the study by telephone, conduct preliminary screening according to the inclusion and exclusion criteria, and then, if appropriate, arrange the acupuncture specialist for face-to-face baseline visit at an appropriate time, meanwhile the subjects will receive radiographic evaluation. The investigator will introduce the research protocol (i.e., the research purpose, procedures and time commitment and potential risks and benefits related to the research) in detail to potential subjects and obtain written informed consent. The subjects’ privacy information will be protected. Each subject will be given a unique random number as a direct identifier of the case report.

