### Interventions

2.8

The treatment plan of the trial is based on the traditional moxibustion in the clinical treatment of KOA, combined with the characteristics of Jade moxibustion instrument itself, considering the standardized requirements of the trial design.

According to the literature review, the following 5 acupoints are selected for each treatment.ST35, ST34, EX-LE4, SP10, and Ashi point (i.e., tender point around the knee joint) are all located in the knee region, and they are common acupoints in the global clinical research of treating KOA.^[28]^ In anatomy, Acupuncture point ST35 and EX-LE4 are located close to the thinnest part of the knee joint, so the thermal effect of moxibustion and Jade moxibustion can directly reach the articular cavity. According to the biomechanical study, most of the clinical diagnosis and treatment guidelines of KOA pay special attention to the muscle strength training of quadriceps femoris.^[29–32]^ The muscle strength of extensor and flexor groups of knee joint is closely related to the symptoms of KOA.^[33]^ SP10 and ST34 are near the area of vastus medialis obliquus and lateral great respectively, so they may directly improve the state of quadriceps femoris. Ashi point is the most painful point according to the actual situation of the subjects.

Subjects are allowed to take concomitant medication, but we will encourage them not to change their medications during the trial. At the same time, other therapies are not allowed, such as acupuncture, sodium hyaluronate injection.

The treatment process will be supervised throughout by the staff of the research team. The two groups of subjects will be treated separately by the rigorously trained treatment operator.

Jade moxibustion Group

The Jade Moxibustion group will use the HX001 temperature-controlled energy knee pads produced by Jiaxing Fuqiduo Thermal Bed Co., Ltd. Jade kneecap will be electrified and preheated for 3 minutes until the temperature rises to 46°C, press the jade in the kneecap against the knee which can be fixed on the knee of the subject. If the patients felt burning at the skin, the temperature will be adjusted.

Traditional moxibustion group

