### Sample size

3.5

There is study indicates that at least a 36% increase in WOMAC score is considered effective.^[36]^ In the previous study of the research group, the average effective rate of the Jade moxibustion group was 55.56%, compared with 46.51% in the traditional moxibustion group. Based on the results of our pilot study and previous reports, we used non-inferiority test to calculate the sample size (α = 67 per group) with α = 0.025, 1−β = 80%, and a cutoff of 0.5. In other words, we expect a sample size of 62 subjects per group to be sufficient to detect statistically significant differences between the 2 groups. There were no cases of shedding in the 2 treatment groups in the previous trial. In order to prevent the occurrence of shedding resulting in insufficient sample size (preset 10% shedding rate), we will recruit 74 subjects for each group, and a total of 148 subjects need to be recruited.

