### Statistical analysis

3.6

Intention-to-treat analysis is the principle of this study, which includes all subjects in the designated treatment group, as well as subjects who have completed at least one course of treatment. The significant difference level is set to 0.05. The baseline characteristics of subjects will be summarized in both groups. For continuous results, the normal distribution of the data is labeled as the mean (standard deviation). For the main outcome, the remission rate of the fourth week will be calculated and χ^2^ test will be used to compare the Jade moxibustion group with the traditional moxibustion group. For secondary outcomes, unpaired scores including WOMAC pain, functional and stiffness scores, SF-36, expectation and reliability of treatment, and overall treatment outcome will be compared at all follow-up time points in both groups. T-test or Wilcoxon rank sum test will be used to compare continuous variables. We will use SPSS version 22 (IBM SPSS Statistics, NY) for statistical analysis.

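### Hospital is not named as a stratification factor although two hospitals recruit and site is fixed before randomisation: a modest source of chance imbalance that is cheap to remove

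*Protocol article*

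**What the plan says.** Section 2.2 of the protocol article names two centres: "Recruitment will be carried out in Tongren Hospital Affiliated to Shanghai Jiaotong University and Shanghai Pudong Hospital of Traditional Chinese Medicine". One is a university-affiliated hospital, the other a traditional Chinese medicine hospital.

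Section 2.6 gives the order of events. "The subject will first receive a brief phone consultation, after that, the subject will be allocated to the site"; consent, examination and randomisation come after that. Allocation is central: "Only the subject who meet the inclusion/exclusion criteria will be randomized by central network randomization program". Subjects "will be randomly assigned to group A - Jade moxibustion group or group B - traditional moxibustion group in a 1:1 ratio".

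Section 2.7 consists of one sentence on stratification: "The subjects will be stratified according to the number of lesions of the KOA (i.e., dual-joint and mono-articular". Hospital is not mentioned there.

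Section 3.6 fixes the main comparison of the week-4 remission rate. A χ² "test will be used to compare the Jade moxibustion group with the traditional moxibustion group". As written, this test uses neither hospital nor the number of affected knees.

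**The concern.** The article gives stratification its own section and names one factor in it. Hospital is the other obvious candidate. It is known before randomisation, the central program could use it at no extra cost, and the two hospitals are of different kinds. Their patients may differ in familiarity with moxibustion and in what they expect of it. That is a plausible inference; the article does not state it. It has some weight because operators know the allocation (section 4) and WOMAC pain and function are reported by the patient.

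If site is left to chance, the arms may hold different proportions of each hospital's patients. Any difference in response between hospitals then adds noise to the jade-minus-traditional difference. A later analysis plan can add site to the model, but it cannot add a stratification factor once randomisation has begun.

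**Working it through.** The plan gives no figure for site balance, so there is none to reproduce on this point. The sample-size derivation in section 3.5 is a separate matter. Reading its cutoff of 0.5 as a rate-difference margin gives 12 per arm, which is neither the 67 nor the 62 stated. Only the recruitment target is used below.

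**Inputs from the article**
- 148 subjects, 74 per arm (3.5), allocated 1:1 (2.6).
- Expected rates (3.5): "the average effective rate of the Jade moxibustion group was 55.56%, compared with 46.51% in the traditional moxibustion group". The expected difference is 55.56 − 46.51 = 9.05 points.

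**Assumptions (not in the article)**
- Split of patients between hospitals: 74/74, 100/48 or 118/30.
- Difference in response rate between hospitals: 10, 20 or 30 points.
- All 148 subjects are analysed, and number of affected knees is unrelated to hospital.

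**Step 1: chance imbalance in hospital mix.** With 74 of 148 subjects drawn into each arm without control for site, the number from hospital A in one arm is hypergeometric. If hospital A contributes a share π of all subjects, the between-arm difference in its share has

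SD = 2 × √(π(1 − π)/147).

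For 74/74: 2 × √(0.25/147) = 0.0825, or 8.2 points. Tail probabilities are exact hypergeometric sums.

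| Split | SD of difference in share | P(≥10 points) | P(≥15 points) |
|---|---|---|---|
| 74/74 | 8.2 | 25% | 7% |
| 100/48 | 7.7 | 22% | 5% |
| 118/30 | 6.6 | 15% | 2% |

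**Step 2: effect on the rate difference.** Shift = (difference in site share) × (site effect). The 95% range is ±1.96 × SD × site effect. For 74/74 and a 20-point effect: 1.96 × 0.0825 × 0.20 = 0.032.

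| Split | 10-point effect | 20-point effect | 30-point effect |
|---|---|---|---|
| 74/74 | ±1.6 | ±3.2 | ±4.8 |
| 100/48 | ±1.5 | ±3.0 | ±4.5 |
| 118/30 | ±1.3 | ±2.6 | ±3.9 |

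**Step 3: comparison with the ordinary sampling error.** The binomial variances are 0.5556 × 0.4444 = 0.2469 and 0.4651 × 0.5349 = 0.2488, with sum 0.4957. SE = √(0.4957/74) = 0.0818, or 8.2 points. The ±3.2 range is 3.2/8.2 = 0.39 of one SE.

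**Step 4: gain from controlling site.** With a 74/74 split and site effect d, site accounts for 0.25 × d² of the variance in each arm. Removing it from both arms gives:
- d = 0.10: √((0.4957 − 0.0050)/74) = 8.1 points.
- d = 0.20: √((0.4957 − 0.0200)/74) = 8.0 points.
- d = 0.30: √((0.4957 − 0.0450)/74) = 7.8 points.

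For d = 0.20 the variance falls by 0.0200/0.4957 = 4%. That is worth about 148 × 0.4957/0.4757 − 148 = 6 extra patients.

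**The case against.** The strongest reply is that this is chance variation, not confounding. Under central 1:1 randomisation the expected site imbalance is zero, and its spread is already contained in the 8.2-point standard error. This stands. A reader might infer that hospital is mixed with the treatment effect; the documents do not support that.

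A second reply is that site imbalance can be dealt with afterwards. This stands too. Hospital is recorded before randomisation, so a stratified or adjusted comparison is possible whatever the randomisation did. Adjustment for site is often left to an analysis plan, and none is shown here, so its absence from section 3.6 is not a fault in itself. It would be wrong to say that the damage cannot be repaired.

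Third, section 2.7 does not say that its factor is the only one, and an article may condense the set-up of a central program. This stands as a caution: the program may already handle site. A section on stratification that names one factor will nevertheless be read as complete.

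Fourth, the article speaks of recruitment at two hospitals. Treatment at both follows naturally from allocation to a site but is not stated, and no site effect is documented. The sizes above are therefore scenarios.

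A reader might also take the sentence in section 2.8, "The two groups of subjects will be treated separately by the rigorously trained treatment operator", to mean a different operator for each arm, so that operator and treatment could not be told apart. The wording does not establish this. It fits separate sessions with the same trained operator just as well, and the same section says that research staff supervise treatment throughout. Stratifying by hospital would not cure such an arrangement in any case. It justifies a request for clarification and no more.

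**Conclusion.** The point holds as a modest design weakness. The article names one stratification factor and leaves out hospital, which was available before randomisation. Under an even site split there is a one-in-four chance that the arms differ by at least 10 points in hospital mix. The effect on the result is small: a 95% range of ±1.6 to ±4.8 points for site effects of 10 to 30 points, always well inside the 8.2-point standard error. Controlling site would bring that standard error to between 8.1 and 7.8 points.

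The imbalance probabilities rest on 74 per arm and the assumed site splits. The shifts rest also on the assumed site effects, for which the article gives no evidence. The comparison remains valid without the change. The change is worth making because it costs almost nothing.

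**What to change.** - **Section 2.7:** add hospital as a second stratification factor in the central program, beside mono- versus dual-joint disease (2 × 2 = 4 strata). With blocks within strata, site imbalance falls to a few patients at most. If the program already stratifies by hospital, say so.
- **Section 3.6:** carry hospital and number of affected knees into the primary comparison, for example as a Mantel-Haenszel stratified risk difference. An unstratified test would not credit the precision gained by stratifying.
- **Section 2.8:** clarify what treating the two groups separately means for operators.
- **If patients are already randomised:** leave the randomisation as it is and specify the stratified analysis before outcome data are seen. That alone recovers most of the benefit.

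Cost: one setting in the randomisation program and a protocol amendment. The sample size stays at 148. The small downside is four strata instead of two, averaging 148/4 = 37 subjects each.
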